#### Adoption

To assess adoption, we will assess (1) facility readiness to implement the intervention, (2) the proportion of clinics incorporating thermal ablation into routine care through updated policies, and (3) proportion of trained providers performing the single-visit screen-and-treat approach to the screen-eligible women and thermal ablation for screen positive women.

To assess readiness for intervention adoption, we will apply the validated ORIC assessment scale translated into Kiswahili and adapted to the implementation context after each wave begins. ORIC is a 12-item Likert-type scale, broken into domains of change commitment (4 items) and change efficacy (8 items), and has demonstrated reliability, content validity, structural validity, structural invariance, and known-groups validity in field application. We will apply the ORIC to 3 management team members of each intervention facility (*n* = 30) and 6 frontline health workers per intervention facility (*n* = 60). Analysis will test whether sufficient inter-rater reliability and inter-rater agreement exist to aggregate individual responses to the facility level. If tests do not justify aggregation, we will use a measure of intra-facility variability in readiness rather than a facility-level mean in our analysis. The resulting analysis will provide readiness profiles for each facility as they initiate implementation, which will complement adoption, implementation, and effectiveness data in understanding the broader impact of the intervention.

Information on the proportion of clinics incorporating thermal ablation into routine care and the proportion of trained providers performing the SV-SAT approach to the screen-eligible women and thermal ablation for screen positive women will be collected every 2 weeks by the technical assistants during the monitoring visits.

### Implementation

Implementation will be measured at the organizational levels to establish consensus on the core components of the intervention as well as determine the drivers of its implementation success and failure. CFIR will guide our examination of the implementation processes and adaptations across the different facilities as well as document determinants of success and failure. We will conduct small group discussion with health providers (*n* = 3) at each clinic and in-depth interviews with health managers (*n* = 10) and screen-positive women (2 per clinic, *n* = 20) and spread out over the intensive implementation wave. Interviewees will be purposively selected to capture diversity in health facilities (rural vs urban, large vs small size, government facility vs mission facility). Interview guides will include questions adapted from the CFIR question bank (cfirguide.org) to gather data about selected constructs from 4 of the established CFIR domains (Table 2). Outer setting constructs of interest will be captured via fields to identify critical external events. Questions associated with these novel constructs will be piloted for understandability and appropriateness prior to data collection. Constructs of interest may be adapted based on the outcomes of Aim 1.

**Table 2 Tab2:** Potential questions to providers and managers by CFIR construct

Intervention characteristics	
• Relative advantage • Adaptability • Complexity • Perceived scalability	• How does thermal ablation compare to cryotherapy in your setting? • ﻿﻿What kinds of changes or alterations do you think you will need to make to SV-SAT + TA so it will be effective? • ﻿﻿How complicated is use of thermal ablation? • ﻿﻿Do you think TA could be expanded for use in other sites?
Outer setting	
• Patient needs and resources	• How well do you think SVA-SAT + TA will meet the needs of women screening for cervical cancer in your facility? • Have you heard stories about the experiences of participants with the SV-SAT + TA?
Inner setting	
• Structural • Characteristics • Networks • Tension for change • Compatibility • Team characteristics • Collective efficacy	• How will the infrastructure of your facility affect the implementation of SV-SAT + TA? • What kinds of infrastructure changes will be needed to accommodate SV-SAT + TA? • Are meetings such as staff meetings, held regularly? What is discussed? Is there a strong need for SV-SAT + TA? Why or why not? • How well does SV-SAT + TA fit with existing work processes and practices in your setting? What are likely issues or complications that may arise? • What sort of team-based care is provided in the facility? • Is your healthcare team capable of working together to implement new interventions like SV-SAT + TA?
Characteristics of individuals	
• Self-efficacy	• How confident are you that you will be able to successfully implement SV-SAT + TA? • What gives you that level of confidence?
Process	
• Executing • ﻿﻿Champions • ﻿﻿Decision-making	• Has SV-SAT + TA been implemented according to the implementation plan? [If Yes] Can you describe this? [If No] Why not? • Are there people in the facility who are likely to champion the intervention? • How are decisions made in this organization? Who make decisions in this organization?
Characteristics of systems	
• Systems architecture • External funding Agent • Priorities • Strategic policy Alignment • Resource continuity	• How is the health system organized and how does it interact with other systems that contribute to the health of the public and that influence how the CC programs are designed and implemented? • ﻿What are the priorities and perspectives of external donors related to TA and CC in general in-country? • ﻿What policies exist in country that support integration of TA? • What existing or potential funding sources exist to continue and scale TA?

### Fidelity to the intervention (HPV sub-study)

We will assess fidelity to thermal ablation training by assessing for HPV clearance among HPV-positive women. We will collect HPV cervical swab prior to and 6 months post-treatment to assess for clearance of type-specific HPV infection (target 60% HPV clearance) post-treatment on all screen positive women treated with thermal ablation. HPV samples will be shipped to the UW/UON HIV/STD Research laboratory in Mombasa. Assuming at least 200 women consent to the HPV sub-study and 70% of them test positive for HPV prior to thermal ablation (*N* = 140), the largest confidence interval for HPV clearance will be ± 8.1%.

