#### Power and sample size

The stepped-wedge study design is powered based on the primary effectiveness outcome, which is the proportion of screen-positive women who receive same-day treatment. According to data on cervical cancer screening and preventive treatment for Kiambu county from 2017 to 2019, 20% of cervical cancer screening clients who screened positive received cryotherapy or LEEP. Routine data from our proposed study facilities show an average of 30 clients per month screened at each facility in the first 3 months of 2020. Assuming 6-month waves, 30 clients screened per month and a 5% screen positive rate, we expect an average of 9 screen-positive women per facility per wave. Assuming an intracluster correlation coefficient of 0.2, alpha = 0.05, and 20% treatment coverage pre-intervention, we will have 80% power to detect a three-fold increase to 60% treatment coverage with the intervention (R [v 3.6.3] package swCRTDesign [v 3.1]). We estimate that 90% of screen-positive women will be eligible for ablative treatment.

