#### Formation of facility committees

We will convene a committee that will serve an advisory team at the facility level. This committee will work closely with the research team to provide input on on-project implementation processes and receive updates provided by the research team. The research team will liaise with the committees to schedule regularly scheduled meetings. We will evaluate the impact of the intervention on the clinical and implementation outcomes using the RE-AIM framework (Table 1).

**Table 1 Tab1:** Summary of outcomes, by RE-AIM domain

RE-AIM domain	Outcomes	Data source
**Reach**	• Proportion of providers trained and women screened per month	• Abstracted client records • Facility level data
**Effectiveness**	• Number of women screen-positive per month • Treatment completion rate among screen-positive women compared to pre-intervention (primary) • Proportion of women with clearance of HPV 6 months post-receiving TA treatment	• Facility level data • HPV test results from randomly selected women
**Adoption**	• Proportion of selected clinics incorporating thermal ablation into routine care through updated policies • Proportion of trained providers performing SV-SAT + TA • Facility readiness	• Facility level data, Technical assistance reports • ORIC scores
**Implementation**	• Core components of the SV-SAT + TA • Description of drivers of success/failure using CFIR constructs of interest	• Facility level data, Technical assistance reports • Key informant interviews
**Maintenance**	• Proportion of clinics that continue to provide and sustain SV-SAT + TA services 12,18, and 24 months after intervention implementation	• Facility level data

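### The HPV sub-study's largest half-width of ±8.1% is a simple binomial figure at 60% clearance with full follow-up; the 200 women behind it are not derived from the planning volume, and two sampling rules conflict

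*Protocol article*

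**What the plan says.** The section on fidelity to the intervention (HPV sub-study) uses HPV clearance after thermal ablation to judge fidelity to the training, with a "target 60% HPV clearance". On timing: "We will collect HPV cervical swab prior to and 6 months post-treatment". On who is sampled: "on all screen positive women treated with thermal ablation". On size: "Assuming at least 200 women consent to the HPV sub-study and 70% of them test positive for HPV prior to thermal ablation", hence N = 140, for which "the largest confidence interval for HPV clearance will be ± 8.1" per cent.

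Table 1, in the effectiveness row, gives the data source as "HPV test results from randomly selected women".

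The section on power and sample size takes 30 women screened per facility per month and 5% screen-positive, so "we expect an average of 9 screen-positive women per facility per wave". It estimates that 90% of screen-positive women can have ablative treatment. The Effectiveness section sets a 60% treatment target that counts any procedure. The Setting section lists, as a site eligibility criterion, a screening volume above 1000 over four months.

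**The concern.** A stated upper limit on interval width is a promise about what the sub-study can show. Three things make this one doubtful.

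- The figure matches a calculation at one particular clearance rate, not the worst case. It leaves no room for women who miss the second swab or for similarity among women treated in the same clinic. The measure is meant to reflect how well training was taken up clinic by clinic, so variation between clinics is part of what is being measured.
- The protocol does not say how 200 is reached, and the one place that derives a screen-positive count points lower at the treatment target.
- The two descriptions of who is swabbed define different samples.

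At stake is how firmly an observed clearance rate can be set against the 60% target. The primary outcome is not affected.

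**Working it through.** **1. Reproducing the stated figure.** Inputs from the HPV sub-study section: 200 × 0.70 = 140; target clearance 0.60. Half-width = 1.96 × √(p(1−p)/n).

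- p = 0.60, n = 140: 1.96 × √(0.24/140) = 8.1%. This is the plan's number.
- p = 0.50, n = 140: 1.96 × √(0.25/140) = 8.3%. This is the largest value at that n.

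Other interval methods at 50% do not give 8.1% either: Wilson 8.2%, Clopper-Pearson 8.6%, continuity-corrected 8.6%. So the plan's figure is a Wald interval at the target, with no design effect and nobody lost.

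**2. Missing 6-month swabs.** No loss rate is stated; these are illustrations at p = 0.50.

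| Assumed loss | n | Half-width |
|---|---|---|
| 10% | 126 | ±8.7% |
| 20% | 112 | ±9.3% |
| 30% | 98 | ±9.9% |

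**3. Clustering by clinic.** No ICC is stated for clearance; again illustrations, at p = 0.50 with no loss. Average cluster size m = 140/10 = 14; design effect = 1 + (14 − 1) × ICC.

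| Assumed ICC | Design effect | Half-width |
|---|---|---|
| 0.01 | 1.13 | ±8.8% |
| 0.05 | 1.65 | ±10.6% |

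**4. Where 200 would come from on the power section's volume.**

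- Time after start: 6 months of intensive support plus 18, 12 or 6 months of maintenance (Provision of technical assistance) = 24, 18 or 12 months for waves 1, 2 and 3.
- Ten clinics, three or four per wave: from 3×24 + 3×18 + 4×12 = 174 to 4×24 + 3×18 + 3×12 = 186 facility-months.
- Screen-positives: 9 per 6 months = 1.5 per month; 174 × 1.5 = 261 to 186 × 1.5 = 279.
- Treated by any procedure at 60%: 157 to 167, even with full consent.
- HPV-positive at 70%: 110 to 117.
- Half-width at p = 0.50: ±9.4% to ±9.1%, before loss or clustering.

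**5. What would remove the shortfall.**

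- Eligibility volume in Setting: 1000/4 = 250 per month; × 0.05 = 12.5 screen-positives per facility-month; × 174 to 186 = 2175 to 2325; × 0.6 = 1305 to 1395 treated.
- More screening at 60% treated: 200/(0.6 × 0.05 × 186) = 36 to 200/(0.6 × 0.05 × 174) = 38 per facility-month, against 30 planned.
- More treatment at the planned volume: 90% of 261 to 279 = 235 to 251 eligible women; 200/251 = 80% to 200/235 = 85% of them ablated and consenting.

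**6. Sampling rule.** The sub-study text takes every screen-positive woman treated with thermal ablation. Table 1 takes a random selection. Both cannot describe the same sample.

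**The case against.** The strongest reply has four parts.

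- *The word largest can be read kindly.* With at least 200 women and clearance fixed at 60%, the smallest sample gives the widest interval. That reading is fair, and the gap to ±8.3% is under 0.2 percentage points. But the sentence does not fix the clearance rate, and N falls below 140 as soon as a swab is missed.
- *The interval method may sit in an analysis plan not shown.* True of the method. It does not rescue a numerical limit that the protocol itself states.
- *The 200 may well be reached.* The 30 per month is routine data from early 2020. The Reach section expects more screening, outreach is planned before training, and 60% is a target, not a ceiling. This stands: a reader might infer that 200 is unattainable, and the documents do not support that. In the other direction, the 60% includes cryotherapy and LEEP, and full consent is assumed, so 157 to 167 is generous for thermal ablation at that volume and target.
- *Larger losses of precision rest on borrowed inputs.* This also stands. A reader might apply the protocol's ICC of 0.2 and obtain ±15.7%, but that value is given for treatment coverage, not HPV clearance. A reader might also count only women treated at least 6 months before maintenance ends (103 to 113 treated, 72 to 79 HPV-positive), but the sub-study section does not tie the second swab to that date.

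**Conclusion.** The stated limit is wrong as worded. ±8.1% is the half-width at the 60% target; the maximum at N = 140 is ±8.3%, and any loss or positive correlation within clinics takes it further. Taken one at a time, the illustrative ranges are ±8.7 to 9.9% for 10 to 30% loss and ±8.8 to 10.6% for an ICC of 0.01 to 0.05. Their size is assumed; their direction is not.

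The 200 is unsupported by the power section's volume at the 60% target: 157 to 167 treated and 110 to 117 HPV-positive, or ±9.1 to 9.4% before loss or clustering. This is a failure to reconcile figures, not proof of a shortfall, because the eligibility volume in Setting conflicts with the power section and would remove it. For the same reason it does not follow that there are too few women to draw a random sample from.

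The contradiction between the sub-study text and Table 1 needs no assumption. The point concerns a secondary sub-study and should be corrected.

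**What to change.** 1. Delete the word largest, or quote ±8.3% at 50% clearance for N = 140.
2. Restate the precision as a range, with the assumed 6-month loss and ICC written beside it.
3. Estimate clearance with an interval that accounts for clinic, with a small-sample correction because there are only ten.
4. Reconcile the screening volumes in Setting and in the power section, and show how 200 is reached from volume, treatment rate, share given thermal ablation and consent. Do not write the 157 to 167 in as the expected sample until that is done.
5. State one sampling rule, in the same words, in the sub-study section and in Table 1.

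The cost is wording, a short calculation and a less favourable stated precision. None of these changes in itself requires more participants or tests.

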### Maintenance

In the first 6 months of implementation in each wave, we will have bi-monthly on-going technical support to health facilities. Thereafter, we will reduce visits to once a month among clinics that meet metrics for transition, and we will then discontinue routine technical assistance visits, but only respond to facility requests as needed. Over this time, research staff will continue to abstract individual level programmatic data. We will continue to monitor the proportion of screen-positive women who complete treatment. In addition, we will monitor the frequency of facility committee meetings. We anticipate that facilities will continue to implement the intervention because we will have utilized a participatory approach that builds ownership and organizational commitment and results in implementation of an intervention that is contextually fit.

### Aim 3. Assess the budget impact of the intervention compared to single-visit, screen-and-treat method using cryotherapy

We will quantify and compare the costs of the intervention to the costs of the current recommended standard practice of SV-SAT with cryotherapy. Using micro-costing techniques, we will estimate the programmatic costs of each strategy, including implementation costs. We will use these data to estimate the cost per woman treated under each strategy, and we will incorporate reach and effectiveness outcome data (from Aim 2) in a decision analysis model to estimate and compare the costs incurred and averted. Cost and impact data will be used to estimate the budget impact of SV-SAT with each treatment strategy. Our primary analyses will take the programmatic perspective, and secondary analyses will include costs incurred by patients to access services and duration of time used by providers to provide services. Our approach, analyses, and results reporting will align with published economic evaluation guidelines, which will maximize the transparency and generalizability of our findings to other settings [31, 32]. We hypothesize that SV-SAT with VIA and thermal ablation will cost less per woman screened and treated and will increase the affordability, feasibility, and impact of cervical cancer prevention relative to SV-SAT with cryotherapy.

### Micro-costing procedure

To capture heterogeneity in costs and efficiency across settings, we will collect cost data in a representative sample of six reproductive health clinics. We will use an activity-based micro-costing approach to measure start-up, implementation, personnel, supply, capital, overhead, and patient costs in each clinic with standard practice (SV-SAT with cryotherapy) and with implementation of the intervention (Table 3). Measured costs will include those incurred in the initial screening and treatment visit as well as follow-up visits. Following published protocols, we will observe clinic visits using time-driven activity-based costing (TDABC) methods to map out and quantify the time spent on each component activity [33]. We will also conduct semi-structured interviews with staff and key personnel to inform estimates of the time and costs required for provision of relevant SV-SAT services. TDABC and interview data will be used to estimate the personnel time required for different cadres of personnel, which will be translated into costs based on average salaries. Start-up costs, ongoing implementation costs, and other program costs will be obtained from project expense reports, clinic records, Ministry of Health (MOH) records, and published literature, as in previous studies [21, 34,35]. Patients will be asked about out-of-pocket expenses and time losses, with time losses translated into costs using data on local wages.

**Table 3 Tab3:** Summary of cost measures and associated data sources

Cost type	Elements	Data sources
Start-up	Training materials: training expenses (trainer fees, staff time spent in training)	Project expense reports; project staff/civil service salaries
Implementation	Ongoing training expenses; technical assistance support, facility committee meetings, fidelity monitoring; community outreach	Project expense reports
Personnel	Time/salaries of healthcare personnel, laboratory personnel, supervisors, and administrative staff	TDABC observations, staff interviews, civil service salaries
Patient	Transportation expenses; other out-of-pocket expenses, including childcare; time losses	Patient surveys, local average wages
Supplies	Consumables such as acetic acid, CO_2_ or N_2_O refrigerant gas, specula, anesthesia, equipment maintenance; transportation costs	Clinic and project expense reports; MoH records
Capital	Liger thermal ablator; cryotherapy machine; laboratory equipment; vehicles	Clinic and project expense reports; MoH records
Overhead	Utilities; clinic maintenance	Study clinic records and expense reports; staff interviews

We will summarize data on costs to estimate the total cost of the intervention per woman. Our micro-costing approach will allow us to identify and exclude costs specific to research activities, focusing only on programmatic costs. To reflect variable costs and activities in different phases of implementation of the intervention, we will stratify costs by initial start-up, implementation and maintenance phases. For each strategy, we will break costs down into the categories in Table 3, above, to identify the key cost drivers. Costs will be discounted at 3% per year, and we will explore alternative discounting rates of 5% and 0%.

### Budget impact analysis procedure

To account for differences in reach and effectiveness by treatment option, we will develop a decision tree model to estimate the expected number of CIN2 + and cervical cancer cases that would arise with SV-SAT with thermal ablation relative to SV-SAT with cryotherapy given the size of the eligible patient population in Kenya. To estimate these health outcomes, we will incorporate study data on reach and effectiveness with each strategy (Aim 2) and published data on HPV natural history and progression to cancer. Costs will be estimated using study data on the cost per woman screened and treated with the intervention and published data of the costs of cervical cancer screening and treatment. To account for variability and uncertainty in key parameters, we will conduct sensitivity analyses by jointly varying these parameters within observed or probable ranges. The model will be programmed using TreeAge Software (Williamstown, MA) [35]. Using data on current Kenya MOH expenditures, we will estimate the budget impact of the two interventions from the MOH perspective. This analysis will reflect the opportunity costs incurred by delivery of the intervention as well as costs averted through prevention of cervical cancer cases.

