#### Data collection and abstraction

The data on facility-level infrastructure including availability of equipment, supplies, and current staffing (numbers, cadre and training) and patient flow will be obtained. Infrastructure supplies and staffing data collection will be collected at three time points in the ten RH study facilities; before and after each implementation wave and at the end of the maintenance phase. Routine data on the proportion of women screened, screened positive, and treated for abnormal lesions will be abstracted monthly, by research staff, covering a minimum period of 6 months prior to introduction of the intervention at any facilities and continuing through the end of the maintenance phase. During pre-implementation periods, clinics will contribute data to the “control” condition in the stepped wedged trial.

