### Aim 2: implement the intervention and evaluate clinical and implementation outcomes using the RE-AIM framework

#### Overview

At 10 reproductive health clinics in central Kenya, we will introduce the intervention and site-specific implementation strategy developed in Aim 1 in a stepped-wedge fashion and rigorously evaluate how effectively this strategy is disseminated and implemented. In three successive 6-month waves, we will roll out the intervention at three to four clinics. A maintenance phase of varying lengths will be conducted across all waves.

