#### Provision of technical assistance

We will provide bi-monthly technical support from the study team with assessment of fidelity and tailoring of the implementation strategy for 6 months at all sites. Depending on their wave assignment, sites will move to a maintenance phase of 18 (wave 1), 12 (wave 2), or 6 (wave 3) months of length as described in Fig. 1. Services provided during the intervention phase include bi-monthly supervision, data collection support, equipment and supplies related to the intervention, and ongoing clinical training for new staff. After the intervention phase bi-monthly, supervision is no longer provided but we will offer intermittent training where necessary and continue data collection. In Aim 2, reproductive health clinics will implement the intervention with the implementation strategy developed and refined at the year 1 stakeholder meeting. We expect that implementation strategies across the 10 sites will include some common and some site-specific components. During the 6-month intervention period, facilities will be supported by the study team to iteratively tailor their implementation strategy using their IRLM conceptual map and identified and prioritized strategy components. Any subsequent adaptations to the site-specific implementation strategies during the intervention period will be documented through use of the FRAME-IS tool [33] including collation of what is modified, the timing of the modification, and the actors and action targets of the modification.

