### Effectiveness

We will assess effectiveness by determining whether the intervention is associated with an increase in the number of screen-positive women identified per month and proportion of screen-positive women who complete treatment (target = 60%) comparing pre-implementation period to intervention periods. This will include women treated with thermal ablation, cryotherapy, LEEP, or any other procedure.

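### Aim 3 presents its result as thermal ablation versus cryotherapy, but Aim 2 supplies only a supported package versus prior routine care, so the device's share of any gain is not identified

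*Protocol article*

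**What the plan says.** All references are to the protocol article.

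**Aim 3.** The introduction to Aim 3 compares the costs of the intervention "to the costs of the current recommended standard practice of SV-SAT with cryotherapy". It hypothesises that SV-SAT with thermal ablation will cost less per woman and have more impact than SV-SAT with cryotherapy. Under Budget impact analysis procedure the purpose of the model is given as "To account for differences in reach and effectiveness by treatment option, we will develop a decision tree model", which then projects CIN2+ and cancer cases under the two options. On inputs it says that "we will incorporate study data on reach and effectiveness with each strategy (Aim 2"), alongside published natural-history data.

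**Aim 2.** The Overview says "we will introduce the intervention and site-specific implementation strategy developed in Aim 1 in a stepped-wedge fashion". Data collection and abstraction gives the comparator: "During pre-implementation periods, clinics will contribute data to the" control condition of the trial. Provision of technical assistance states "Services provided during the intervention phase include bi-monthly supervision, data collection support, equipment and supplies related to the intervention", plus training for new staff. The Training section adds hands-on training, a VIA refresher and community outreach, and Formation of facility committees adds an advisory committee. On the effectiveness outcome, which compares the pre-implementation period with the intervention periods: "This will include women treated with thermal ablation, cryotherapy, LEEP, or any other procedure".

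**Costs.** Aim 3 includes implementation costs for each strategy. Table 3 lists training, technical assistance, committee meetings, fidelity monitoring and outreach among them.

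**The concern.** Aim 3 needs reach and effectiveness for two treatment options. Aim 2 observes two conditions, and they differ in much more than the device. Fed into the model as the text describes, the whole before-to-after gain would be credited to the choice of thermal ablation over cryotherapy, including whatever part comes from training, outreach, supplies and supervision.

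This matters because the Background offers the findings as evidence for national policy, and the Discussion says they will support decisions on resources for both provider training and equipment. Those are two of the components that the contrast cannot separate. A ministry reading a result labelled by device could expect the device alone to deliver what the package delivered.

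**Working it through.** The plan states no figure for this contrast, so there is none to reproduce. The check sets the two aims side by side and then shows how wide the unidentified range is.

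**Step 1. What changes at the step, and what is measured**

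- Device: thermal ablation is introduced (Overview).
- Support: training and VIA refresher, outreach, supervision, supplies, a facility committee and a site-specific strategy come with the same roll-out (Training; Provision of technical assistance; Formation of facility committees; Overview).
- Comparator: routine data from the same clinics before the step (Data collection and abstraction).
- Outcome: treatment by any procedure, in either period (Effectiveness).

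No clinic-period has cryotherapy with the support, or thermal ablation introduced without it. Device and support are therefore collinear in every clinic, and no analysis of Aim 2 can separate them. Reach has the same problem, because outreach and training belong to the same roll-out. The planned comparison of the intensive and maintenance phases (Data analysis) shows what happens once regular supervision is reduced. It still contains no supported cryotherapy condition.

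**Step 2. Size of the unidentified range**

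Inputs from Power and sample size: 20% coverage before the intervention (county routine data, cryotherapy or LEEP) and 60% with it. The 60% is a planning value and a target, not an estimate. Let c be the coverage that cryotherapy would reach with the same support; c is an assumption.

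- Whole contrast per 1000 screen-positive women: 1000 × (0.60 − 0.20) = 400 more treated.
- Part due to the device: 1000 × (0.60 − c).
  - c = 0.20: 1000 × 0.40 = 400
  - c = 0.40: 1000 × 0.20 = 200
  - c = 0.60: 1000 × 0 = 0

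Aim 2 data are compatible with any of these.

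**Step 3. Direction of the error in the budget result**

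Suppose, for simplicity, that device and support add. Let D and S be their effects, K_D and K_S their costs, and A(·) the later costs averted.

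- Modelled net budget: K_D + K_S − A(D) − A(S).
- Device-only net budget: K_D − A(D).
- Difference: K_S − A(S).

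The health gain attributed to the device is too large if the support works (S > 0). The net budget can err either way, depending on whether the support costs more or less than it averts. The documents give neither quantity.

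**The case against.** The strongest reply is that a budget impact analysis properly compares a new programme with current practice. Aim 3 names current practice as its comparator and counts start-up, implementation and maintenance costs, so package effects are set against package costs. The Background hypothesis also joins the intervention to its tailored strategies. This stands: package versus current practice is a legitimate question. It does not support a label by treatment option, and the article elsewhere treats the intervention and the implementation strategy as separate things.

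The Background also blames cryotherapy's gas supply, equipment cost and equipment failure for low treatment, so part of the gain may be a true device effect. That stands too. The same passage lists turnover of trained staff, which is not specific to a device, so the split remains unknown.

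Sensitivity analyses over plausible parameter ranges are planned, and an article may leave their details to the full plan. But varying inputs does not change which contrast the base case is said to estimate.

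A reader might infer more than the documents support:

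- *That separate, unsupported clinics serve as controls.* They do not; control data come from earlier periods of the same ten clinics.
- *That the clinics lack cryotherapy.* Eligibility in Setting requires VIA and does not mention cryotherapy, but Training says some providers are trained in it, and Micro-costing procedure plans to cost it as standard practice.
- *That an HPV clearance figure available only for thermal ablation tilts the model.* The sub-study measures clearance only after thermal ablation, and Table 1 lists it under effectiveness, but the budget impact section does not say that clearance enters the model.
- *That the budget result must favour thermal ablation.* Support costs are counted, so its net direction is open.

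**Conclusion.** The point holds as one of attribution. The text on Aim 3 promises a difference between treatment options that Aim 2 cannot deliver. What Aim 2 delivers is the effect of the supported package with thermal ablation compared with prior routine care.

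On the planning figures, the device's part lies anywhere from 0 to 400 of 400 additional women treated per 1000 screen-positive. That range assumes the 60% target is met and that equally supported cryotherapy would reach between 20% and 60%. It shows lack of identification and does not measure a bias. The primary trial comparison and the sample size are unaffected.

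**What to change.** In the introduction to Aim 3 and in Budget impact analysis procedure:

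1. Define the base case as the implementation package with thermal ablation versus observed pre-implementation routine care. Reword the hypothesis to match and remove the treatment-option wording.
2. Add a scenario in which cryotherapy receives the same support and carries its costs, with its reach and treatment completion varied from the observed pre-period values to the observed post-period values. Confine any statement on thermal ablation versus cryotherapy to this scenario.
3. If post-treatment clearance or cure enters the model, take it from comparable sources for both devices.

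The cost is revised wording and one more set of model runs, with no new data collection. The price is that the device-specific result becomes a range and may look less favourable.
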